##### 5. Economic assessment

The economic evaluation will be a cost-utility analysis conducted from the perspective of the UK National Health Service, assessing the incremental quality adjusted life years (QALYs) gained and incremental cost to the NHS from the MoleMate system versus current best practice. The incremental cost-effectiveness ratio will be calculated, and appropriate analysis of uncertainty will be undertaken. Drawing on the trial and other epidemiological and cost data from the literature, the analysis will be conducted over a 10 year time horizon, and based on a decision tree, defined at the point of analysis.

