## Background

### 1.1 Melanoma and health policy

Suspicious pigmented lesions (SPLs), or 'moles' are a common presenting problem in general practice consultations, and while the majority are benign, a small minority are malignant melanomas. Melanoma is a serious skin cancer, accounting for less than one in ten skin cancers, but responsible for 2% of all cancers and 1% of all cancer deaths in the UK, with around 9,500 new cases and 1,800 deaths a year (Cancer Research UK). Worldwide, the incidence of melanoma is increasing faster than any other cancer, with an approximate doubling of rates every 10-20 years in countries with white populations [1]. While the incidence in the UK is one of the highest in Europe, it is lower than the reported incidence from other countries such as Australia and New Zealand, which lead the world age-standardised rates at about 50 per 100,000 population per annum [2] (compared with 11.9 per 100,000 population in the UK (Cancer Research UK)). Furthermore, although the incidence of melanoma increases with age, a third of all cases occur in people aged less than fifty years and it is the second most common cancer in the 20-39 age group. The increasing incidence has been attributed to increases in ultra-violet exposure, both natural and artificial. Other risk factors include genetic predisposition reflected in the phenotypic features of multiple moles, fair complexion, sunburn-susceptible skin types, and family history. In the UK, melanomas are more common in women than in men, although the prognosis is poorer for men over 60 years who tend to present with thicker melanomas [3].

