Early detection is critical in reducing mortality and morbidity from melanoma, as thin lesions (Breslow thickness less than 1 mm) have a five-year survival of over 95%, compared to less than 50% for thicker lesions (Breslow thickness more than 4 mm). There is evidence from the UK that expert consultation within 2 weeks of referral results in thinner tumours and improved overall survival [4]. The Department of Health's recent Cancer Reform strategy highlighted the issues of poor public awareness of cancer symptoms, diagnostic delays in primary care and late diagnosis across all cancers. In response, the National Awareness and Early Diagnosis Initiative was jointly launched by Cancer Research UK and the Department of Health in 2008 [5] with two of the seven key objectives being to develop interventions to promote early presentation and reduce diagnostic delays in primary care.

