### 2.5 Patients

Patients are eligible for the trial if aged 18 years or over, able to give informed consent, and have a pigmented lesion (either presented by the patient or noticed by a health care professional) which is not immediately diagnosed as benign and the patient reassured. These patients are given an appointment with a Lead Clinician within one week and provided with information about the MoleMate Trial prior to formal consent and recruitment by the Lead Clinician.

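### The fixed 10-year horizon of the cost-utility analysis leaves out life-years after year 10 and so understates the survival part of the QALY difference, roughly 2- to 4-fold under assumed age mixes.

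*Protocol article*

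**What the plan says.** Section 2.11 of the protocol article, under 5. Economic assessment, plans a cost-utility analysis for the NHS, "assessing the incremental quality adjusted life years (QALYs) gained and incremental cost to the NHS", summarised as an incremental cost-effectiveness ratio (ICER). It fixes the horizon: "the analysis will be conducted over a 10 year time horizon". The inputs are not confined to trial data: "Drawing on the trial and other epidemiological and cost data from the literature". The decision tree is to be specified when the analysis is done, and an analysis of uncertainty is promised without details.

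Section 1.1 gives the facts that bear on the horizon:

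- On survival, "thin lesions (Breslow thickness less than 1 mm) have a five-year survival of over 95%, compared to less than 50% for thicker lesions" (the latter being those above 4 mm).
- On age, "a third of all cases occur in people aged less than fifty years". Melanoma is also said to rank second among cancers in young adults, aged 20 to 39.

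Section 2.5 sets a lower age limit and no upper one: "Patients are eligible for the trial if aged 18 years or over". Registry follow-up for melanoma incidence and mortality is five years (section 2.9.2).

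**The concern.** A diagnostic aid that leads to earlier or later detection of melanoma changes QALYs largely through deaths averted or caused. A person whose death is averted in the first few years is usually alive at year 10 and may live for decades more. A model that stops at year 10 gives those later years no value. The omission runs in one direction: it shrinks a survival gain if MoleMate finds melanomas earlier, and it shrinks a survival loss if MoleMate misses them. Varying parameters inside a 10-year model does not show this.

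The stake is the cost-utility conclusion, which the Discussion and Conclusions present as evidence to inform new service models.

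**Working it through.** The plan states no QALY or ICER figure, so there is nothing to reproduce. The question is what share of the life-years at issue falls within 10 years.

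**Simple check.** Suppose a melanoma death at year *d* is averted or caused in someone with *L* years of life remaining. With annual discount rate *r* and v = 1/(1+r), the share counted by year 10 is (1 − v^(10−d)) / (1 − v^(L−d)), or (10−d)/(L−d) without discounting. *L*, *d* and *r* are assumptions; the protocol gives none of them.

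| L | d | share, 0% | share, 3.5% |
|---|---|---|---|
| 15 | 4 | 6/11 = 0.55 | 0.59 |
| 20 | 2 | 8/18 = 0.44 | 0.52 |
| 30 | 4 | 6/26 = 0.23 | 0.32 |
| 40 | 6 | 4/34 = 0.12 | 0.19 |

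**Fuller check.** This uses the protocol's survival figures and lets background mortality act.

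- Excess melanoma hazard per year is −ln(S5)/5. For thin lesions (S5 = 0.95) this is 0.0103; for thick lesions (S5 = 0.50) it is 0.1386. It is applied for 5 or 10 years and is zero afterwards. The 95% and 50% come from section 1.1, where they are bounds; the duration is an assumption.
- Background hazard is Gompertz, A·exp(0.095 × age), with A = 0.00002 or 0.00003. This is an assumption. It gives about 30 to 34 years remaining at age 50, 18 to 21 at 65 and 8 to 11 at 80.
- The gain is the discounted area between the thin and thick survival curves, summed by month to year 10 and to age 110. The factor R is the lifetime gain divided by the 10-year gain.
- The age mixes are assumptions, each with equal thirds so that one third is under 50: central (40, 60, 75) and older (45, 70, 80).

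| Case | R at 0% | R at 3.5% |
|---|---|---|
| Central mix | 3.2 to 4.2 | 2.2 to 2.7 |
| Older mix | 2.7 to 3.5 | 2.0 to 2.4 |
| All aged 70 | 1.9 to 2.5 | 1.6 to 2.0 |
| All aged 80 | 1.3 to 1.7 | 1.25 to 1.5 |

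One cell in full: central mix, 3.5%, excess hazard for 5 years, A = 0.00003. The gain per patient moved from thick to thin is 2.56 discounted life-years by year 10 and 5.70 over a lifetime, so R = 5.70/2.56 = 2.2, and 2.56/5.70 = 45% is counted.

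A smaller shift in survival (95% v 90%) barely changes R: at age 50 with the 5-year excess hazard and A = 0.00003 it is 3.8 undiscounted and 2.6 at 3.5%, against 3.7 and 2.6. An age-related fall in utility to 0.75 also changes it little, for example from 2.22 to 2.16.

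**From life-years to the ICER.** If a share *w* of the 10-year QALY difference is not survival-related (worry, for example) and has the same sign, the total QALY difference grows by w + (1−w)R. With w = 0.25 and R = 2.2 this is 0.25 + 0.75 × 2.2 = 1.9. If incremental cost is positive and costs after year 10 are similar in both arms, a QALY gain understated by this factor overstates the ICER by the same factor.

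**The case against.** The strongest case against the point has four parts.

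- **Age.** Section 1.1 also says that incidence rises with age, so two thirds of cases are 50 or over, and that men over 60 tend to present with thicker tumours. There is no upper age limit. This stands: for older patients the factor falls to two-fold or below, and with 15 years remaining and death at year 4 it is only about 1.7 to 1.8.
- **Other routes to benefit.** MoleMate is meant to reduce benign referrals, and worry is measured as an outcome. Not all of the QALY difference need come from survival. This stands, and it limits what can be said about the ratio.
- **Extrapolation.** Observed follow-up is five years, so a lifetime model leans on assumptions. That is a real cost, but it does not force the cut-off: the 10-year model already runs past the follow-up and draws on the literature.
- **A fuller plan.** The article is a condensed account, and a full economic plan may hold a rationale and other horizons. For that reason the absence of a stated reason is not part of this point. The point is the horizon that the article does fix.

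A reader might also infer that QALYs are truncated while all device and referral costs are charged at the start. The documents do not say so. Section 2.9.2 lists purchase and training, but also recurring maintenance and technical support, GP visits, referrals and excision, and it gives no timing. Costs after year 10 are cut off as well.

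**Conclusion.** The point holds for the survival part of the QALY difference. As written, the 10-year horizon understates it, whether MoleMate gains or loses survival. With one third of cases under 50, the assumed background mortality and discounting of 0 to 3.5%, the lifetime figure is roughly 2 to 4 times the 10-year figure, and about 2.2 to 2.7 times in the central mix at 3.5%. From about age 70 at 3.5% it is no more than about two-fold (1.6 to 2.0 at 70, less at 80). The discount rate, life expectancy and age mix are assumptions; the protocol gives only the survival contrast and the third under fifty.

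Two stronger readings are tempting and are not supported:

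- **That the ICER itself is wrong by two-fold or more.** This would need a QALY difference that is almost all survival, a positive incremental cost and similar costs after year 10 in both arms. If MoleMate saves money and does not lose QALYs, it is preferred under either horizon and the decision does not change.
- **That the understatement reaches about eight-fold.** This needs 40 years remaining, death at year 6 and no discounting, which is a corner case.

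The economic assessment is a secondary analysis. No randomised comparison, no data collection and no part of the primary outcome is affected.

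**What to change.** Attach discounted lifetime QALY and cost payoffs to the terminal nodes of the planned decision tree, make that the base case, and report the 10-year result as a scenario. State the discount rate. Include costs after year 10 in the payoffs so that costs and QALYs cover the same period.

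The cost is a wording change and some extra modelling. The tree has still to be defined, so no built model has to be altered. The downside is added extrapolation uncertainty. The uncertainty analysis already planned can carry it, and the 10-year scenario shows the reader how far the conclusion rests on later years.

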### 2.12 Trial organisation and management

A Trial Steering Committee, consisting of investigators, research team members, expert dermatologists and plastic surgeons, a statistician, a health economist, Biocompatibles plc (previously Astron Clinica) staff, two lay members and an independent chair, has been formed and will meet annually for the duration of the trial.

## Discussion

This trial is designed to estimate the effect of the MoleMate intervention, compared with current best practice, on the management of suspicious pigmented lesions in general practice, as reflected in the appropriateness (PPV) of referrals to a skin cancer clinic. As such, we are considering the MoleMate system as a diagnostic tool and testing its effectiveness in the hands of primary care clinicians. There has been increasing interest in clinical decision support (CDS) aids in recent years, and they range from electronic texts, drug information and practice guideline databases to rules-based guidance systems that direct clinicians about exactly what to do for specific clinical problems. The MoleMate system is a good example of a CDS aid, with the incorporation of an algorithm specifically developed for use in primary care, with a new imaging technology already increasingly used by dermatologists. The MoleMate system has been developed to extend the utility of SIAscopy from differentiating melanoma from other pigmented lesions in the secondary care setting, to differentiating 'suspicious lesions' from 'non suspicious lesions' in the primary care setting.

The trial seeks to address a common challenge for primary care health professionals- how to recognise and appropriately manage the rarely-presenting but serious conditions from commonly-presenting benign conditions. Differentiating melanomas from other pigmented lesions in primary care is particularly challenging, even among men aged over 60 years more than 99.7% are estimated to remain benign [6], and 95% of all lesions currently referred to a specialist prove to be benign [10]. The development and rigorous evaluation of tools such as the MoleMate system to assist clinical decision making in primary care is one approach to maximising referral efficiency, and as such meets one objective of the National Awareness and Early Diagnosis Initiative [5].

The measures and interventions for the MoleMate UK Trial have been developed using the approach defined by the MRC Framework for development of complex interventions for evaluation in randomised trials [27,28] to ensure rigour, transparency and reproducibility. The four-month pilot phase confirmed the proposed recruitment and referral rates and the feasibility of participant randomisation. It demonstrated the feasibility of tracking referred participants in secondary care, and established mechanisms for reference standard diagnosis for all lesions recruited into the trial. During the pilot phase semi-structured interviews and questionnaires confirmed that both participants and lead clinicians found all aspects of the trial process, including randomisation, were acceptable and did not appear to cause distress. However, we await data from the main trial on the psychological impact of trial participation and acceptability of the MoleMate system.

This trial tests a novel service model of internal referral in general practice to Lead Clinicians who do not have dermatological training. We are conducting an economic evaluation of the use of the MoleMate system within this service model to establish its cost-utility compared with current best practice.

Our primary outcome measure is based on the clinical significance of a lesion, as determined by the actual management (biopsy or monitor) by a skin cancer specialist. This is a meaningful outcome in terms of health service delivery and the need to improve referral efficiency. While ideally we would have detection of melanoma as the primary outcome, this would require a much larger trial to have sufficient statistical power. We will capture data on melanoma incidence and mortality in all participants over 5 years. This will provide important data on the false negatives; lesions incorrectly diagnosed as benign.

## Conclusions

In conclusion, this is the first randomised controlled trial in general practice of a decision aid using SIAscopy for the assessment of pigmented skin lesions. Preliminary data from diagnostic validation studies in the UK and Australia suggest the MoleMate system is reasonably sensitive and specific but only an RCT can determine its effect on clinical management in the UK setting. If the trial demonstrates that using the MoleMate system improves diagnostic efficiency, it will add to the range of approaches to support assessment of pigmented skin lesions in UK primary care. If the trial provides evidence of cost-utility it will inform new service models to reduce referrals to secondary care of benign lesions and improve the early diagnosis of melanoma.
